## Abstract

**Background:**

Hand osteoarthritis is a common and disabling chronic joint disease with a lack of effective therapies. Emerging evidence suggests the role of local inflammation in causing pain in hand osteoarthritis. Corticosteroids are potent anti-inflammatory drugs used in many rheumatic diseases. The aim of this randomised, double-blind, placebo-controlled trial is to determine whether topical corticosteroid reduces pain over 6 weeks in patients with hand osteoarthritis.

**Methods:**

One hundred participants with hand osteoarthritis will be recruited from the community in Melbourne, Australia, and randomly allocated in a 1:1 ratio to receive either topical Diprosone OV or placebo ointment administered 3 times daily on the painful hand joints for 6 weeks. The primary outcome is pain reduction (assessed by 100 mm visual analogue scale) at 6 weeks. The secondary outcomes include changes in pain and function assessed using Functional Index for Hand Osteoarthritis, Australian Canadian Osteoarthritis Hand Index, Michigan Hand Outcomes Questionnaire, and tender and swollen joint count at 6 weeks. Adverse events will be recorded. The primary analysis will be by intention to treat, including all participants in their randomised groups.

**Discussion:**

This study will provide high-quality evidence to determine whether topical corticosteroid reduces pain over 6 weeks in patients with hand osteoarthritis, with major clinical and public health importance by informing clinical practice guidelines for the management of hand osteoarthritis and reducing the burden of the disabling disease.

**Trial registration:**

Australian New Zealand Clinical Trials Registry (ANZCTR), ACTRN12620000599976. Registered 22 May 2020.

**Supplementary Information:**

The online version contains supplementary material available at 10.1186/s12891-021-04921-2.

## Background

Hand osteoarthritis (OA) is a common chronic joint disease causing pain, functional disability, and decreased quality of life which result in substantial burden of disease [1, 2]. The lifetime risk of symptomatic hand OA is 39.8% in the general population, 47.2% for females and 24.6% for males [3]. In people aged 55 years and over, 67% of the women and 54.8% of the men have radiographic OA in at least one hand joint, with 20% having disabling pain [4]. Hand OA impairs the activities of daily living such as dressing and eating [5], with significant clinical importance in relation to health-related quality of life [2]. The healthcare costs for treating this condition are expected to escalate due to the ageing population and increasing obesity [6]. Disease-modifying drugs for hand OA are currently not available. In terms of clinical guidelines for the management of hand OA, the European League Against Rheumatism suggests topical therapy (non-steroidal anti-inflammatory drugs (NSAIDs) being first-line choice), oral analgesics (e.g. paracetamol and NSAIDs), and non-pharmacological therapy (education, assistive devices, exercises and orthoses) [7]. The American College of Rheumatology conditionally recommends management with topical capsaicin, topical NSAIDs, oral NSAIDs, as well as non-pharmacological therapy [8]. Although there is some evidence for at best, a short-term moderate effect of topical and oral NSAIDs on pain alleviation, evidence is conflicting for the efficacy of anti-inflammatory medications, such as corticosteroids and biologic agents [9]. There is an unmet need for effective therapies for hand OA.

Increasing evidence suggests that hand OA is a disease of the whole joint with local inflammation playing an important role in causing pain and disease progression [1]. Imaging studies have shown that most patients with hand OA have synovitis (~ 50%) [10, 11], and that painful joints are more likely to have synovitis than non-painful joints [10, 12, 13]. Moreover, synovitis has been shown to be the strongest predictor for progression of structural damage in hand OA [14–17]. Therefore, inflammation is a potential treatment target in hand OA, and therapies targeting synovitis may provide a novel approach for the management of hand OA. Glucocorticoids are potent multitargeted anti-inflammatory drugs which have been used in many rheumatic diseases because of their anti-inflammatory and immunosuppressive actions [18]. Randomised controlled trials have shown the effect of oral corticosteroids (prednisolone) on reducing pain and improving function in patients with hand OA over 6 weeks [19, 20], with little effect over 3 months [19, 21]. However, systemic corticosteroids are associated with significant adverse events including diabetes and osteoporosis [22, 23]. Intra-articular injections of corticosteroids are effective but the effects often last less than 1 month [24]. It is also technically difficult to perform in small hand joints so often performed under ultrasound guidance which adds significantly to the cost, inconvenience and timeliness of treatment. Topical delivery of corticosteroids provides a potential alternative approach to improving outcomes in hand OA. Topical corticosteroids are safe, inexpensive and commonly used for skin conditions. However, there have been no clinical trials examining the efficacy of topical corticosteroids in reducing pain in hand OA.

### Objectives and hypothesis

We propose a randomised, double-blind, placebo-controlled trial to determine the effect of topical Diprosone OV ointment administered 3 times daily on painful hand joints compared to placebo in reducing pain and improving function in participants with hand OA over 6 weeks. It was hypothesised that topical Diprosone OV ointment would be more effective than placebo in reducing pain and improving function in participants with hand OA over 6 weeks.

### Study design

This is a single center, parallel-group, randomised, double-blind, placebo-controlled trial over 6 weeks.

### Trial registration

The trial was registered at the Australian New Zealand Clinical Trials Registry prior to recruitment commencing (ACTRN12620000599976, registered 22 May 2020). The trial reporting will be guided by the Consolidated Standards of Reporting Trials (CONSORT) Statement [25]. Protocol reporting is in accordance with the SPIRIT Statement (Standard Protocol Items: Recommendations for Interventional Trials) [26].

### Ethics approval

Ethics approval has been obtained from Alfred Hospital Ethics Committee (117/20) and registered at Monash University Human Research Ethics Committee (24219). Written informed consent will be obtained from all the participants.

## Methods

### Study setting and participants

Eligible participants with hand OA will be recruited from the community in Melbourne, Australia via advertisements and from medical practitioners.

#### Inclusion criteria

Participants aged ≥40 years with symptomatic radiological hand OA will be recruited. We will also invite those who contacted us to take part in the clinical trial of methotrexate for hand OA but could not take part due to concern about using methotrexate on the part of the participants or contraindications to its use. As recommended by the Osteoarthritis Research Society International (OARSI) clinical trials guidelines for hand OA [27], a pain score of at least 40 on a 100 mm visual analogue scale (VAS) and radiologic OA (Kellgren and Lawrence grade ≥ 2) in ≥1 hand joint will be required for study entry. Additional inclusion criteria include stable analgesic requirements (including NSAIDs) for at least 4 weeks, stable doses of chondroitin or glucosamine for 4 months, no corticosteroids via any route for at least 3 months.

#### Exclusion criteria

(i) concomitant rheumatic disease, inflammatory joint disease, psoriatic arthritis, ankylosing spondylitis, or gout; (ii) allergic reaction to other medicines containing betamethasone dipropionate, any other corticosteroid(s), or any of the ingredients of Diprosone OV ointment (i.e. betamethasone as dipropionate, propylene glycol, white beeswax, propylene glycol monostearate, and soft white paraffin); (iii) contraindication to topical corticosteroids (e.g. untreated bacterial, fungal, or viral skin lesions; widespread plaque psoriasis; skin conditions with ulcers); (iv) unable to complete informed consent; (v) pregnancy, breast feeding, or trying to become pregnant.

### Study timeline

This trial began recruitment in October 2020. Recruitment is estimated to be completed in January 2022 with the study finalized by 6-week follow-up and data collection in March 2022. Figure 1 shows trial participation and study procedure.

**Fig. 1 Fig1:**
[figure not shown]
Flowchart of trial participation

### Randomisation, allocation concealment, and blinding

Allocation of participants in a 1:1 ratio to either topical corticosteroid or placebo group will be based on computer generated random numbers prepared and securely held by the Alfred Health Clinical Trials Pharmacy. Block randomisation will be performed, stratified by gender given the higher prevalence of hand OA in females compared with males [4]. The use of a central automated allocation procedure with security in place will ensure the allocation cannot be accessed or influenced by any person. Participants, assessors and statisticians will be blinded to group allocation. Allocation concealment and blinding will be ensured by: (1) study medication being dispensed by the Alfred Health Clinical Trials Pharmacy; (2) use of an identical placebo ointment; (3) subjective measures being taken by assessors blinded to group allocation. Emergency unblinding will be allowed in limited situations that impact on the safety of study participants. Code-break for the full randomisation schedule will be maintained by the Alfred Health Clinical Trials Pharmacy, and be used in case of the need for emergency unblinding. Participants who are unblinded will be withdrawn from treatment and be requested to complete questionnaires at 6 weeks.

### Intervention

Participants will be randomised to receive topical corticosteroid or placebo. Placebo will be of the same colour and appearance as the corticosteroid ointment. They are required to apply a thin layer of the study ointment to cover the painful hand joints 3 times per day for 6 weeks.

#### Corticosteroid

Diprosone OV (betamethasone dipropionate in Optimised Vehicle) ointment. Diprosone OV contains the active ingredient betamethasone dipropionate which is a potent corticosteroid used to decrease inflammation, redness, itchiness and discomfort of some skin conditions. Diprosone OV ointment is used to treat persistent or severe dermatitis, eczema, and acute or chronic psoriasis.

#### Placebo

Plain paraffin ointment.

#### Safety

Adverse events will be recorded throughout the study. Photos of the hands, back and front, will be taken at baseline and 6 weeks to be reviewed by a dermatologist for safety check, mainly looking for dilatation of vessels, skin wrinkling, and hypopigmentation. Photos at 3 weeks will be taken and reviewed if there is any concern.

#### Compliance

The remaining ointment will be weighed at the end of the study to document compliance. Weekly telephone contact over the 6 weeks will be conducted to address any concerns. This will help to mitigate non-compliance.

#### Concomitant medication

To maintain the pragmatic nature of the trial, there are no restrictions about the use of concomitant analgesic medications. Participants will be allowed to continue the treatments being taken at the screening visit for the duration of the trial. If a participant is experiencing severe pain and requires an increase in analgesic dose, the use of paracetamol, topical or oral NSAIDs or opioids, or a combination of these will be permitted, with the reason for the dose increase and the dose used to be documented.

### Study procedure

Table 1 shows the study procedure. Volunteers will be telephone screened and undergo an x-ray of the symptomatic hand (standardized posteroanterior view) to confirm radiologic disease. In the case of bilateral symptomatic hands, the most symptomatic hand will undergo x-ray. In the case of both hands being symptomatic to an equal degree, the dominant hand will undergo x-ray. The study visits will be onsite or via telehealth. Consent will be obtained by the study doctor. At baseline, all the hand joints with a pain level of ≥40 on a 100 mm VAS will be documented on a hand map. The participants will be given a copy of this for reference when they are contacted by study staff by telephone. Participant will be asked to apply the study ointment on each of the pre-specified joints 3 times per day for 6 weeks. Participants are able to withdraw at any time during the trial; the time and reasons will be recorded. They will be requested to complete the questionnaires at 6 weeks.

**Table 1 Tab1:** Timetable and measures to be made

	Screening	Double-blind period						
	Screening / baseline assessment	Randomization	Week 1	Week 2	Week 3	Week 4	Week 5	Week 6
**Visit/phone contact**	**0**	**1**	**2**	**3**	**4**	**5**	**6**	**7**
**Informed consent**	X							
**Clinical visit or telehealth**	X							X
**Telephone follow-up**			X	X	X	X	X	
**Hand x-ray**	X							
**Medical history**	X							
**Medication**	X							
**Employment and education**	X							
**Smoking and alcohol**	X							
**Questionnaires**								
Hand VAS	X							X
Hand NRS	X		X	X	X	X	X	X
FIHOA	X							X
AUSCAN	X							X
MHQ	X							X
painDETECT	X							X
**Physical examination**								
Height, weight	X							
Tender/swollen joint count	X							X
**Compliance and safety (adverse events)**			X	X	X	X	X	X
**Hand photos**	X							X
**Dispense medication**		X						

*VAS* Visual analogue scale, *NRS* Numerical rating scale, *FIHOA* Functional Index for Hand Osteoarthritis, *AUSCAN* Australian Canadian Osteoarthritis Hand Index, *MHQ* Michigan Hand Outcomes Questionnaire

### Primary outcome

Pain reduction at 6 weeks will be measured according to the OARSI recommendations for the design and conduct of clinical trials for hand OA, which recommend the use of a single question pain VAS as the main outcome measure for hand pain [27]. VAS has been most frequently used for pain assessment in hand OA, with excellent reliability, good construct validity and sensitivity to change [28].

### Secondary outcomes

#### Pain over 6 weeks

Participant will be asked weekly using a numerical rating scale (NRS) about their pain levels in general as well as in each of the study joints by referencing the hand map that they will have. Time to respond will be recorded.

#### Change in pain and function at 6 weeks

At baseline and 6 weeks, hand pain, physical function, and joint activity will be measured according to the OARSI recommendations [27] using the Functional Index for Hand OA (FIHOA) [29], Australian Canadian Osteoarthritis Hand Index (AUSCAN) [30], Michigan Hand Outcomes Questionnaire (MHQ) [31], and tender and swollen joint count [32].

### Other measures

#### Success of participant blinding

Participants will be asked which treatment they believe they received.

#### Treatment adherence

We will weigh the ointment container before and after the study.

#### Adverse events, analgesic use, and co-interventions

These will be measured in a log-book and by structured questioning by the blinded assessor at each follow-up.

#### painDETECT

*painDETECT*, a validated questionnaire used to assess pain sensitization in OA [33] will be assessed at baseline and 6 weeks.

#### Descriptive data

Self-reported age, gender, height, weight, duration of symptoms, employment, medical history, medication use, education level, smoking, and alcohol will be collected using a questionnaire.

### Sample size calculation

The mean VAS pain in a previous clinical trial of symptomatic hand OA similar to the proposed study was 54 mm (standard deviation 20 mm) [19]. The minimal clinically important difference to be detected in OA trials is a 15 mm change in VAS pain (out of 100 mm) [34]. We will require 40 participants per group to attain a power of 90% to detect the minimal clinically important difference (alpha 0.05, two-sided significance). Accounting for an estimated 20% loss to follow-up, we seek to recruit 100 participants, 50 in each group.

### Statistical analyses

An intention-to-treat analysis, including all participants in their randomised groups regardless of their adherence to assigned treatments, will be performed in a blinded fashion. Pain reduction at 6 weeks will be analyzed using ANCOVA with adjustment for the baseline measure. The bootstrap approach will be used to provide 95% confidence intervals and *p*-values if the normality assumption is questionable. Differences between randomised groups in trajectories of pain over time will be examined using linear mixed-effects regression models with baseline score as the covariate, fixed factors for treatment, time, and treatment x time interaction, and with an autoregressive AR (1) covariance matrix for repeated measures of individuals over time. Time to respond (weeks) will be compared between randomised groups. If more than 5% of participants are missing their primary outcome, multiple imputation will be applied to account for missing data, with missing values imputed separately by treatment group, assuming data are missing at random. Additional adjustment for age, gender, body mass index, and severity of radiographic OA will be carried out in a sensitivity analysis if clinically important baseline imbalances between randomised groups are identified. Pre-specified subgroup analyses will be performed by testing a treatment by subgroup interaction in the models. This will include joint group, radiographic severity, pain level, and presence of central sensitization. Per-protocol analyses for the primary and secondary endpoints will be conducted as secondary analyses.

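### Randomisation is stratified by gender but the primary ANCOVA omits gender; if gender is prognostic beyond baseline pain, the primary test is slightly conservative (minor)

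*Protocol article*

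**What the plan says.** Under Randomisation, allocation concealment, and blinding, the protocol article allocates 1:1 and states: "Block randomisation will be performed, stratified by gender given the higher prevalence of hand OA in females compared with males". Gender is the only stratification factor named, and the reason given is prevalence.

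Under Statistical analyses, the primary model is fixed as follows: "Pain reduction at 6 weeks will be analyzed using ANCOVA with adjustment for the baseline measure". The mixed model for pain over time likewise names the baseline score as its only covariate besides treatment, time and their interaction. Gender appears once in that section: "Additional adjustment for age, gender, body mass index, and severity of radiographic OA will be carried out in a sensitivity analysis", and then only "if clinically important baseline imbalances between randomised groups are identified". If normality is doubtful, "The bootstrap approach will be used to provide 95% confidence intervals" and p-values; the article does not say whether resampling respects the strata.

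**The concern.** The design and the primary model do not match. Blocking within gender keeps the arms close to balanced on gender, so differences between men and women contribute little to the chance variation of the treatment contrast. A model without gender still counts those differences as residual error. Where gender is related to the outcome after allowing for baseline pain, the reported standard error is then larger than the true sampling variation, confidence intervals are wider than needed, and the test rejects less often than its nominal 5%.

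The conditional sensitivity analysis does not repair this. Stratification is there to prevent a gender imbalance, so gender itself should seldom trigger it. If another covariate triggers it, the primary result still comes from the model without gender.

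What is at stake is interval width, which matters most if the result is null or borderline and the question is whether a 15 mm benefit can be excluded.

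**Working it through.** **The plan's own figure.** Inputs from Sample size calculation: difference 15 mm, SD 20 mm, two-sided alpha 0.05, power 90%, 20% loss.

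n per arm = 2 × (1.960 + 1.282)² × 20² / 15² = 37.4, so 38 by the normal approximation; the noncentral t gives 39. The stated 40 gives power of 91.8% (normal) or 91.2% (t). 40 / 0.80 = 50 per arm, 100 in total. The sample size reproduces and is not affected by this point.

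**Assumptions not in the article.** Proportion of women p = 0.75; blocks of 4; correlation r between baseline and week-6 VAS of 0 or 0.5; difference g between women and men in week-6 VAS, beyond baseline VAS, of 0, 5, 10 or 15 mm.

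**Expected ratio of standard errors (without gender / with gender).**

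Ratio = √(1 + g² p(1 − p) / residual variance), where p(1 − p) = 0.1875 and the residual variance is 400(1 − r²), that is 400 at r = 0 and 300 at r = 0.5.

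- g = 5: g² p(1 − p) = 4.69; ratio 1.006 (r = 0), 1.008 (r = 0.5)
- g = 10: 18.75; ratio 1.023, 1.031
- g = 15: 42.19; ratio 1.051, 1.068

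**Simulation.** Gender-stratified permuted blocks, 100 randomised, 80 analysed after random loss, 6,000 trials per row. Monte Carlo error on a 5% rate is √(0.05 × 0.95 / 6000), about 0.3 points. In each cell the planned model comes first and the model with gender second. Mean SE is from the runs with no treatment effect; power is for 15 mm.

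| r | g (mm) | Mean SE (mm) | Type I error | Power |
|---|---|---|---|---|
| 0 | 0 | 4.49 / 4.50 | 5.2% / 5.3% | 90.6% / 90.3% |
| 0 | 5 | 4.52 / 4.50 | 4.7% / 4.7% | 90.8% / 91.0% |
| 0 | 10 | 4.60 / 4.50 | 4.5% / 4.9% | 89.2% / 90.0% |
| 0 | 15 | 4.71 / 4.49 | 4.0% / 4.7% | 89.0% / 91.0% |
| 0.5 | 0 | 3.89 / 3.89 | 5.1% / 5.0% | 96.6% / 96.5% |
| 0.5 | 5 | 3.93 / 3.91 | 4.6% / 4.9% | 96.6% / 96.7% |
| 0.5 | 10 | 4.01 / 3.89 | 4.4% / 4.8% | 95.8% / 96.4% |
| 0.5 | 15 | 4.16 / 3.90 | 3.9% / 4.9% | 95.3% / 96.6% |

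The simulated SE ratios agree with the formula: 4.16 / 3.90 = 1.07 and 4.01 / 3.89 = 1.03.

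**Reported SE against true variation.** At r = 0.5 and g = 15, the planned model reports a mean SE of 4.16 while its estimates have an empirical SD of 4.01, a ratio of 1.04. This is smaller than 1.07 because random loss lets a little gender imbalance back in. A z-test with its SE 1.037 times too large has type I error 2 × [1 − Φ(1.96 × 1.037)] = 4.2%, in line with the simulated 3.9%.

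**Sensitivity to the gender mix.** An even split is the least favourable. At r = 0.5, g = 10 gives type I error of 4.5% and g = 15 gives 3.6%, the latter with an SE ratio of 4.24 / 3.90 = 1.09.

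**The case against.** The strongest objection is that the consequence is conditional. A reader might infer that the primary test is conservative as a matter of fact. The article does not support that: it stratifies because hand osteoarthritis is commoner in women, which concerns who enrols, not how their pain responds. It gives no gender difference in week-6 VAS. With g = 0 the two models agree (5.1% and 5.0% at r = 0.5), and at g = 5 the departure from 5% is within about two Monte Carlo errors. This part of the objection stands.

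The upper end of the range is also demanding. A 15 mm difference between men and women beyond baseline pain equals the whole minimal clinically important difference used to size the trial, and amounts to about 10% of the variance (42.19 / 400). That stands too.

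A reader might also square the SE ratio, (4.16 / 3.90)² = 1.14, and conclude that about 12% of the sample is wasted (1 − 1/1.14). That describes the width of the reported interval in the most extreme 75%-women scenario. Stratification still protects the estimate itself, and the power cost there is 1.4 points at r = 0.5 and about 2 at r = 0.

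It might further be said that covariates belong in the statistical analysis plan. That does not answer the point: the article names the primary covariate and assigns gender to a conditional sensitivity analysis, so it has made the choice. It does not list the predictors for multiple imputation, however; that is ordinary analysis-plan content and is not criticised here.

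**Conclusion.** The mismatch between stratified design and unstratified primary analysis is explicit in the article. If gender predicts week-6 VAS beyond baseline VAS, the model-based standard error is somewhat too large and the test slightly conservative; if not, nothing changes.

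Under the stated assumptions (75% women, blocks of 4, r from 0 to 0.5, g from 0 to 15 mm), the SE is about 0 to 7% larger than it need be, type I error is about 4 to 5%, and power falls by about 0 to 2 points, to 89% at the lowest. An even gender split would stretch the extreme case only a little.

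The error is on the safe side: a positive result would not be undermined, the sample size stands, and validity is not threatened. The point is minor, and worth making because the remedy is nearly free.

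**What to change.** Replace the primary-analysis sentence with wording such as: *VAS pain at 6 weeks will be analysed by ANCOVA with terms for treatment, baseline VAS and gender (the stratification factor).* The gender term should not depend on observed imbalance. Include gender in the same way in the secondary-outcome models and the mixed model for pain over time. If the bootstrap is used, resample within gender strata so that it mirrors the randomisation. The conditional sensitivity analysis can stay for age, body mass index and radiographic severity.

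The cost is a short text change and one degree of freedom. No new data are needed, since gender is required for randomisation and is already listed under Descriptive data. If gender proves unrelated to outcome, the loss is negligible: at g = 0 the mean SE is 3.89 with or without it (r = 0.5). The change should be made before unblinding.

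### The secondary weekly pain model uses one baseline slope for all six weeks; a baseline by week term would sharpen the trajectory comparison at almost no cost

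*Protocol article*

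**What the plan says.** Under the secondary outcome Pain over 6 weeks, the protocol article states: "Participant will be asked weekly using a numerical rating scale (NRS) about their pain levels in general", and also in each study joint. Table 1 marks the hand NRS at baseline and at each of weeks 1 to 6.

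The Statistical analyses section compares the arms' pain trajectories with a linear mixed-effects model "with baseline score as the covariate, fixed factors for treatment, time, and treatment x time interaction". The same sentence gives a participant's weekly scores a first-order autoregressive, AR(1), covariance. The baseline score enters once, as a main effect.

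The primary outcome has its own model: "Pain reduction at 6 weeks will be analyzed using ANCOVA with adjustment for the baseline measure".

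**The concern.** A baseline main effect without a baseline by time term assumes that baseline pain predicts week 6 as strongly as week 1. Serial pain scores often lose correlation as the gap widens, and choosing AR(1) for the follow-up weeks is in that spirit. If baseline behaves likewise, the pooled slope is too small in week 1 and too large in week 6.

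Two things follow. Week-specific contrasts, and above all the change in treatment effect across weeks, are less precise than the collected data allow. And, given the particular baseline imbalance that randomisation produced, the adjustment error moves from one sign early to the other sign late. That is the shape of a treatment by time difference, which this model is meant to detect. Randomisation is stratified by gender only, so balance in baseline pain is left to chance.

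**Working it through.** **Inputs from the protocol article.** SD 20 mm and target difference 15 mm on the VAS, 40 per group after dropout, 50 per group randomised (Sample size calculation); 1:1 allocation; weekly scores at weeks 1 to 6.

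**Assumptions.** The article gives neither a week-to-week correlation nor an NRS SD. I take ρ from 0.5 to 0.95, with and without a stable between-person share c of 0.3 to 0.5; unit SD at every time point, converted at 20 mm; and complete data.

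**The plan's own figure.** n = 2(1.960 + 1.282)² × (20/15)² = 37.4, so 38 per group (39 with the t distribution). The stated 40 gives about 91% to 92% power, and 40/0.8 = 50. The sample size reproduces and is not in question.

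**Slopes.** If baseline is time 0 of the same process, the right slope at week t is s_t = c + (1 − c)ρ^t. The single slope is the generalised least squares average, b = [s₁ + s₆ + (1 − r)(s₂ + s₃ + s₄ + s₅)] / [2 + 4(1 − r)], where r is the fitted AR(1) parameter. At ρ = 0.8, c = 0, r = 0.734: b = [1.062 + 0.266 × 1.889] / 3.064 = 0.51, against right slopes running from 0.80 to 0.26.

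**Effect at one week.** Given the imbalance d in mean baseline, the treatment estimate at week t is shifted by (s_t − b)d. Its variance is proportional to (1 − s_t²) + (s_t − b)²; the second part disappears with a baseline by week term. At ρ = 0.8:
- Week 1: 0.36 + 0.289² = 0.444, ratio 1.23; SE 2.98 mm against 2.68 mm.
- Week 6: 0.931 + 0.249² = 0.993, ratio 1.07; SE 4.46 mm against 4.32 mm.

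**Effect on the week-6-minus-week-1 contrast.** Here b cancels, so the result does not depend on how the slope is pooled. The drift is −(s₁ − s₆)d, and the excess variance is (s₁ − s₆)². At ρ = 0.8 the needed variance is 0.931 + 0.360 − 2(0.328 − 0.210) = 1.055 and the excess is 0.538² = 0.289. The ratio is 1.27 and the SE is 5.19 mm against 4.59 mm (40 per arm).

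| ρ, stable share | right slope, week 1 → 6 | week-1 SE | week-6 SE | contrast variance | drift for d = 0.3 SD |
|---|---|---|---|---|---|
| 0.5, 0 | 0.50 → 0.02 | +6% | +1% | +14% | 0.15 SD |
| 0.7, 0 | 0.70 → 0.12 | +10% | +3% | +26% | 0.17 SD |
| 0.8, 0 | 0.80 → 0.26 | +11% | +3% | +27% | 0.16 SD |
| 0.9, 0 | 0.90 → 0.53 | +9% | +2% | +20% | 0.11 SD |
| 0.95, 0 | 0.95 → 0.74 | +6% | +1% | +11% | 0.06 SD |
| 0.7, 0.3 | 0.79 → 0.38 | +7% | +2% | +17% | 0.12 SD |
| 0.7, 0.5 | 0.85 → 0.56 | +5% | +1% | +11% | 0.09 SD |
| 0.5, 0.5 | 0.75 → 0.51 | +3% | under 1% | +6% | 0.07 SD |
| constant 0.6 | 0.60 → 0.60 | 0 | 0 | 0 | 0 |

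For a more persistent pattern, correlation 0.35 + 0.45 × 0.7^k at lag k, simulated standard errors were 1.5% larger at week 1 and under 1% larger at week 6. The drift for 0.3 SD was about 0.08 SD. In every case the variance of the six-week average changed by about 0%.

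**How likely is the imbalance?** Its SE is √(2/n) SD. With 50 per arm, z = 0.3/0.200 = 1.50 and P = 13%. With 40 per arm, z = 0.3/0.224 = 1.34 and P = 18%.

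**Error rates.** In 600 simulated null trials per setting, the joint 5-df treatment by time test rejected in about 5% without the term. Among trials with imbalance beyond 1.5 SE (about 80 of 600, so imprecise), it rejected in 10% to 13% without the term and 4% to 7% with it. In 1,000 simulated trials per setting with an effect building from 0 to 0.75 SD, the term raised the joint test's power from 62% to 67% at ρ = 0.8 and from 56% to 57% at ρ = 0.7.

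**The case against.** The strongest reply is that the plan is consistent with itself. A reader might infer that AR(1) and a constant baseline slope contradict each other, since both stand in one sentence. They do not: with baseline as a covariate, the AR(1) matrix describes weeks 1 to 6 given baseline and says nothing of how baseline correlates with each week. That stands. Fading from baseline is a reasonable expectation, not something the article states.

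A mixed-effects model may also carry a participant effect, so that correlation levels off. That stands too. It shrinks the effect, as the rows with a stable share show, but removes it only if the correlation with baseline is the same at every week.

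The 15 mm target belongs to the week-6 VAS, not to an NRS trajectory, so it is a poor yardstick for the drift. Against the contrast's own SE of about 5 mm at ρ = 0.8 with 40 per arm, a drift of 0.16 SD (3.2 mm at SD 20 mm) is less than one SE.

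Finally, a constant baseline slope is a common and valid specification, and a condensed article may leave interactions to the full plan. But the article does list the fixed effects, and the point addresses that list. If the full plan already has the term, nothing need change.

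**Conclusion.** The point holds as an efficiency improvement to a secondary analysis. If the correlation of baseline with later scores fades, the listed model gives the week-6-minus-week-1 contrast about 6% to 27% more variance than needed. It also leaves a drift of about 0.06 to 0.17 SD (1.3 to 3.5 mm at SD 20 mm) when baseline differs by 0.3 SD. The size rests on an assumed correlation and on borrowing the VAS SD for the NRS; under constant correlation it is zero.

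A reader might infer that the trajectory analysis is biased or has an inflated false-positive rate. The calculations do not support that: estimates are unbiased over repeated randomisations and the joint test stays near 5%. The distortion is conditional on the imbalance that happens to occur. The simulated rate for the week-6-minus-week-1 contrast alone was 6% at ρ = 0.8 and 9% at ρ = 0.9 without the term, but the article does not single out that contrast. Nor is the trial's main conclusion at risk, since the primary ANCOVA fits its own baseline slope at week 6.

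**What to change.** In the secondary weekly NRS model, list the fixed effects as baseline score, week (categorical), treatment, treatment by week, and baseline score by week. Report the week-specific and averaged treatment contrasts from that model. Settle this before unblinding, so that no trajectory difference has to be argued over afterwards.

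The cost is one line of wording and about 5 degrees of freedom out of roughly 480 weekly scores (80 participants × 6 weeks). It needs no new data and loses no precision of note if the term proves unnecessary.
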